## Methods

### Study design

This study will use a quasi-experimental design with an interrupted time-series analysis to compare three years pre (2022–2024) and post (2025–2027) intervention. The intervention will involve training ASP teams and surgeons in facilitation strategies in addition to conducting order set review and modification. We hypothesize that a combined order set and facilitation training will result in a significant reduction in excessive post operative prophylaxis use, by fostering better engagement between ASP teams and surgeons, such as helping negotiate different communication styles and understanding of relevant data presentation. The primary endpoint of the study is the percentage of inappropriate antibiotic use. Secondary endpoints will investigate change in SSI and CDI rates.

The Nationwide Children’s Hospital Institutional Review Board (IRB) has deemed this study non-human subjects research (IRB #: STUDY00004505). An information sheet will be provided to adult ASP team members and surgeons completing the surveys. The Standard Protocol Items: Recommendations for Interventional Trials (SPIRIT) Checklist guided the development of this protocol manuscript [19].

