##### Hospital survey

Each participating hospital will be required to complete a characteristics survey, to be filled out by the ASP team member most familiar with the hospital. This survey will collect data on hospital size (e.g., number of beds, surgical volume) and details about the ASP program, including the strategies implemented, locations of implementation (e.g., intensive care units, emergency department), and evaluation metrics used. Additionally, the survey will gather specific information on ASP efforts to reduce post-operative antibiotic use in various surgical subspecialties.

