##### Order sets review

To evaluate Behavior and Results domains of our evaluation model, an assessment will be conducted through 10-min structured interviews approximately 6-, 12-, and 18-months post-workshop training. An interview guide is provided in Supplementary File 2. Based on our experience from our Operatic 1.0 trial, this time interval is sufficient for ASPs to implement order set modifications across different surgical specialties, and participants are generally able to recall the work they have accomplished. The interview will inquire whether an order set modification was made, or a new order set developed (Yes/No, and number). For each impacted order set, we will inquire about the targeted procedure, the previous duration (no post-op antibiotics, 24 h or less, 25–48 h, or 48 h or more), and any changes in duration (eliminated, shortened, or no change). If the post-operative duration has been shortened, we will specify to what extent: no post-op antibiotics, 24 h or less, or 25–48 h. We anticipate some loss to follow-up due to staff turnover. In such cases, we will attempt to identify an alternative respondent, describe the study, and determine whether guideline integration through order set changes has continued.

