### Clinical outcomes

#### Primary hypothesis

We hypothesize that the appropriately lagged post-intervention percentage of cases receiving unnecessary postoperative antibiotic prophylaxis will be significantly lower than in the pre-intervention period. To test this hypothesis, we will use an intention-to-treat approach for the primary analysis, including all complete case patient data from the NSQIP-P analysis set. A mixed-effects logistic interrupted time series (ITS) regression model will assess the impact of "order set change resulting in reduction" (1) versus "no order set change" (0) on prophylaxis prescriptions. The model will include the intervention (pre vs. post), time (in months), and an interaction term between time and intervention, including a random intercept to account for intra-hospital correlation in the model. The post-intervention slope (β_2) will be the primary estimate of interest (Fig. 2), but we will also investigate differences at 12, 24 and 36 months. The interruption point will be 12 months after each hospital’s first training, with sensitivity analyses at lags 9, 15, and 18 months as well. We will extend the model to adjust for age, surgical subspecialty, procedure type, hospitalization duration, and co-morbidities using Akaike information criterion (AIC)-based variable selection. Subgroup analyses by procedure type and hospital will also be conducted.

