A key strength of this study is its multi-center design, which enhances the generalizability of findings across diverse hospital settings. The inclusion of at least 20 hospitals participating in both the SHARPS Collaborative and NSQIP-P ensures that the intervention is tested in varied environments with different levels of ASP maturity and institutional support. Additionally, the use of a time-series analysis allows for the evaluation of long-term trends and the sustainability of the intervention’s effects. However, this study has potential limitations. The quasi-experimental design and interrupted time series analysis, while robust, do not entirely eliminate the possibility of confounding variables that may not have been captured or controlled for in our hospital demographics and individual participant characteristics, potentially influencing the observed outcomes. Additionally, reliance on NSQIP-P data for clinical outcomes may introduce delays in data availability. Another challenge is participant attrition, particularly in follow-up interviews assessing long-term implementation outcomes. While targeted recruitment and incentives will be used to mitigate this issue, some loss to follow-up is expected. Lastly, because this study is mostly conducted in tertiary-care children's hospitals, its findings may not be generalizable to other clinical settings, such as community hospitals.

The results of this study will inform future efforts to refine and optimize ASP facilitation strategies. If successful, the training model could be expanded to other pediatric and adult surgical settings, with potential adaptations based on specialty-specific prescribing patterns. This study represents a significant step toward improving antibiotic stewardship in pediatric surgery by addressing both the technical and relational aspects of implementation. The findings will provide critical evidence for disseminating and implementing facilitation and order set modifications to de-implement unnecessary post-operative antibiotics at children's hospitals in the United States.

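### The ITS uses trained hospitals only, with no comparison series, so co-interventions starting near or after a hospital's interruption point cannot be separated from the training

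*Protocol article*

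**What the plan says.** The Study design section states: "This study will use a quasi-experimental design with an interrupted time-series analysis to compare three years pre" (2022–2024) with three years post (2025–2027). Under Clinical data, NSQIP-P cases are requested from hospitals that took part in the workshop, so the analysis set holds no untrained hospitals.

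Under Primary hypothesis, "The model will include the intervention (pre vs. post), time (in months), and an interaction term between time and intervention", plus a random intercept for hospital. "The interruption point will be 12 months after each hospital’s first training", with sensitivity lags of 9, 15 and 18 months. The post-intervention slope is the primary estimate, and differences at 12, 24 and 36 months are also examined. Candidate adjusters are age, subspecialty, procedure type, length of hospitalization and comorbidities. The same section mentions a 1/0 indicator for order set change, but it is not among the listed model terms.

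Other stewardship activity appears in the Hospital survey section, under Baseline data, which collects "specific information on ASP efforts to reduce post-operative antibiotic use in various surgical subspecialties". For follow-up at 6, 12 and 18 months, the Order sets review section says: "The interview will inquire whether an order set modification was made, or a new order set developed". The Data collection section adds facilitation techniques. No repeat of the hospital survey is described.

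The Discussion concedes that the design and analysis "do not entirely eliminate the possibility of confounding variables that may not have been captured" or controlled for through hospital demographics and participant characteristics.

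**The concern.** Each hospital is compared only with its own past. An ITS removes a pre-existing trend that continues, but not another event that begins around the interruption. Such events are plausible here. Hospitals volunteer from a stewardship collaborative or a surgical quality programme, the baseline survey itself expects them to have other efforts on this same outcome, and the 12-month lag leaves time for something else to start.

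The order-set indicator does not fill the gap, because it is determined by how a hospital responded to training and so is not an untrained control. Nor does the adjustment set: its variables describe the case, and none records concurrent stewardship activity. The hospital and participant characteristics that the Discussion refers to are not among the model terms listed.

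At stake is attribution. The article intends its results as evidence for disseminating the training. A fall caused by a separate local programme could be reported as the training's effect, and the data needed to tell the two apart might not have been collected.

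**Working it through.** The plan gives no figure for this bias, so there is none to reproduce. Its power statement is not an input. The check asks what the stated model returns when the training does nothing and something else lowers use.

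**Inputs from the protocol article**
- Pre-intervention rate 45%, 20 hospitals, 14 procedures per hospital per month (Power and sample size calculations).
- 72 months, 2022–2027 (Study design).
- Interruption at training + 12 months (Primary hypothesis).
- Two roll-outs: two hospitals a month (power section), or quarterly sessions over two years (Workshop content and delivery).

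**Assumptions**
- True training effect zero.
- First training in January 2025 (month 36, counting January 2022 as month 0).
- An abrupt, lasting co-intervention that lowers use by 5 points, from 45% to 40%.
- Expected values are fitted, without sampling noise, and hospital intercepts stand in for the random intercept.
- The slope is the change in trend at the interruption, per year.

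**Full credit.** The odds ratio of the co-intervention itself is (0.40/0.60) / (0.45/0.55) = 0.6667/0.8182 = 0.815. A fitted value of 0.815 means wholly credited to training, and 1.00 means not credited.

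**Stated model (linear time).** The 12-month OR is step OR × slope OR. For example, for month 54 with monthly entry, 0.883 × 0.942 = 0.832.

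| Co-intervention starts | Monthly entry: step / slope / 12-month | Quarterly entry: step / slope / 12-month |
|---|---|---|
| Everywhere, month 36 (Jan 2025) | 0.994 / 1.056 / 1.049 | 1.013 / 1.034 / 1.048 |
| Everywhere, month 42 | 0.938 / 1.040 / 0.975 | 0.971 / 1.025 / 0.996 |
| Everywhere, month 48 | 0.871 / 1.017 / 0.886 | 0.919 / 1.012 / 0.930 |
| Everywhere, month 54 | 0.883 / 0.942 / 0.832 | 0.912 / 0.965 / 0.880 |
| Everywhere, month 60 (Jan 2027) | 0.996 / 0.857 / 0.854 | 0.940 / 0.918 / 0.863 |
| Locally, training + 6 months | 0.888 / 1.027 / 0.912 | 0.879 / 1.020 / 0.897 |
| Locally, training + 12 months | 0.815 / 1.000 / 0.815 | 0.815 / 1.000 / 0.815 |

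On the step and the 12-month contrast, credit runs from none to full. On the slope, common starts at months 36 to 48 push slightly against the training, and only the starts at months 54 and 60 favour it.

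**Same model with calendar-month effects.** Every common-date start returns 1.000 for step, slope and 12-month contrast under both roll-outs, because hospitals not yet past their interruption act as concurrent controls. A local start at training + 12 months still returns 0.815. Calendar effects therefore deal with common-date events but not with local ones.

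**Illustration only, not model output.** If half the hospitals start a programme worth 10 points, the average series falls by 0.5 × 10 = 5 points, the same size as the power section's target difference read as percentage points. A quarter of the hospitals gives 0.25 × 10 = 2.5 points. If the starts in half the hospitals are spread evenly over 24 post-interruption months, the drift is 5/2 = 2.5 points per year, and that does enter the slope.

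**Is a within-hospital comparison feasible?** Clinical data gives up to 1,500 cases a year per hospital: 1,500/12 = 125 a month across all wound classes, against 14 spine procedures a month in the power section. The order set interviews record which procedure was targeted. The clean and clean-contaminated share is not stated, but untargeted cases should be plentiful.

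**The case against.** The tempting stronger reading is that any co-intervention starting in 2025–2027 is credited to the training. The documents do not support it. The interruption is specific to each hospital, entry is staggered, the pre-trend is modelled and the lag is varied. Under the assumptions above, a common start in January 2025 biases against the training, one in July 2025 is nearly neutral with quarterly entry, and an abrupt local start at the interruption leaves the primary slope at 1.00.

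Three further points stand:
- The interview guide (Supplementary File 2) is not shown, so one cannot say that later efforts are never recorded, only that the article does not describe it.
- The quarterly collaborative meetings follow from completing the training and belong to the intervention. Efforts begun after training may be its intended result.
- Targeted procedures may differ from untargeted ones: in the earlier trial teams were encouraged to pick procedures they thought could be changed. A rival programme could also aim at the same ones. An untargeted-procedure series cannot settle attribution alone.

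It is also fair that residual confounding is disclosed and that subgroup analyses by procedure type and hospital are planned. These could hint at a fall common to all procedures, but they are not a formal contrast, and the disclosure does not name concurrent stewardship activity.

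**Conclusion.** The point holds in limited form. The stated model has no comparison series and no calendar-period term, and the article describes recording of other efforts only at baseline. Co-interventions that start near or after a hospital's interruption point therefore cannot be separated from the training.

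Depending on timing they are credited wholly, partly or not at all. This mainly affects the step and the 12-, 24- and 36-month contrasts, and reaches the primary slope in the training's favour only when starts are late or spread over the post period. The sizes rest on an assumed 5-point co-intervention, assumed start dates and a January 2025 first training. A reader might take the 5-point example from half the hospitals as the expected bias, but it is a raw level shift under assumption.

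This is a known weakness of uncontrolled ITS with an inexpensive partial remedy. It should be acted on, but it does not invalidate the study.

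**What to change.** 1. Pre-specify a supportive controlled ITS that compares procedures targeted for order set change with untargeted clean and clean-contaminated procedures in the same hospital and months. Report the difference in pre/post change beside the primary result, not in place of it. State three limits: targeted procedures are chosen as modifiable, spill-over makes the contrast conservative, and a rival programme aimed at the same procedures is not removed.
2. Repeat the hospital survey item on other efforts at 6, 12 and 18 months, with start dates and whether each effort arose from the training. Add a sensitivity analysis that censors a hospital only at the start of a programme that did not arise from the training. Count the quarterly collaborative meetings as part of the intervention.
3. Add a sensitivity model with calendar-period effects that uses the staggered entry, to remove common-date events.

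Cost: a little more analysis on data already requested, one interview item, and supportive estimates that are less precise than the primary one. The interview item is the urgent part, because start dates not collected during follow-up may not be recoverable at analysis.

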### Study setting and participants

This study will be conducted at a minimum of 20 children's hospitals and will recruit from either members of the SHaring Antimicrobial Reports for Pediatric Stewardship (SHARPS) Collaborative [20, 21] or the National Surgical Quality Improvement Program-Pediatric (NSQIP-P) [22, 23]. Founded in 2013, SHARPS aims to improve antimicrobial use across healthcare settings and includes over 70 hospitals with dedicated antimicrobial stewardship teams [20]. NSQIP-P, with 156 participating hospitals, collects data on surgical procedures, including prophylactic antibiotic administration, to enhance pediatric surgical care [22]. ASP teams and surgeon champions from 20 hospitals will be recruited to participate in the updated facilitation workshop via live webinar or asynchronous online at least version. Recruitment will be facilitated through the SHARPS Collaborative Listserv and NSQIP-P webinars, which reach over 150 hospitals. Primary participants will be ASP team members, with extended eligibility for infectious diseases fellows, NSQIP-P surgical leads, surgical clinicians, and surgical fellows.

### Conceptual frameworks and logic model

Our study is guided by the i-PARIHS framework (Integrated Framework for Promoting Action on Research Implementation in Health Services), which facilitates the implementation of evidence-based practices [15, 24]. This framework, used in various clinical settings and informed by our previous Operatic 1.0 trial, posits that successful implementation depends on the quality of evidence, the context, and the facilitation process [15, 25, 26]. The four key constructs are: innovation (evidence quality), recipients (those affected by the evidence), context (the setting for implementation), and facilitation (the active process of integrating evidence into practice). For this study, we focus on contextual factors at both the hospital and surgical specialty levels, as these are where ASP activities are primarily implemented. A description of the variables characterizing the core constructs for this study is provided in Table 1. Successful evidence implementation requires facilitation strategies that assess and respond to both the evidence and recipients within their specific context. In our study, facilitation will be carried out by antimicrobial stewards who will use targeted strategies to enable the uptake and integration of evidence-based practices.

**Table 1 Tab1:** Core i-PARIHS constructs

Innovation	Recipients	Context	Facilitation
1. Current antibiotic prophylaxis guidelines 2. Local prescribing & infection rates 3. Alignment of evidence with local priorities	1. Section Chiefs 2. Surgeons 3. Patients 4. Supportive staff	1. Resources 2. Culture 3. Evaluation Receptivity 4. Leadership	1. Antimicrobial Stewards 2. Order set review & modification 3. Recipient engagement

Figure 1 illustrates our implementation research logic model for improving antibiotic prescribing practices through a virtual facilitation workshop and order set modifications. The model highlights key contextual factors, including resources, culture, leadership, and receptivity, while identifying key actors such as surgical section chiefs, surgeons, and supportive staff. The intervention addresses barriers, promotes evidence-based practices, and fosters stakeholder engagement using antibiotic prescribing guidelines and ASP. Outcomes are categorized into proximal implementation outcomes (acceptability, satisfaction, and knowledge and skills acquisition), distal implementation outcomes (order set adoption and reach, appropriate antibiotic prescribing and usage), and clinical outcomes (SSI and C. diff rates).

**Fig. 1 Fig1:**
[figure not shown]
Implementation research logic model of proposed study

### Facilitation workshop

#### Workshop updates and adaptation

In the first six months of the study, we will refine and consolidate our baseline order set and facilitation workshop to enhance scalability and accessibility. Participant feedback from our Operatic 1.0 trial has identified key improvements, including more team-based discussions, additional materials, reduced time commitment, and alignment with the latest evidence on de-implementation, facilitation, and surgical prophylaxis. To improve feasibility and dissemination, we will incorporate continuing medical education (CME) credits through Nationwide Children’s Hospital’s CME department, and offer a self-paced, asynchronous format alongside the live webinar. To address concerns about the workshop’s time demands (previously eight hours over four weeks), we aim to streamline it to three hours delivered in just one session instead of four. We will pre-record didactic content and seek permission to share interactive elements, such as role-playing exercises, ensuring a balance between structured learning and collaboration.

#### Workshop content and delivery

This workshop is designed to build facilitation skills in the context of de-implementation within ASPs. Drawing on real-world data and evidence-based strategies, the session guides participants through a structured exploration of behavior change, communication, and the use of local data to support reductions in post-operative surgical prophylaxis (Table 2). The live workshop combines didactic presentations, hands-on assessments, reflective exercises, and facilitated discussions. Participants will engage with core topics such as evidence-based prescribing practices, data-driven change strategies, hospital context and capacity, and interpersonal dynamics, including communication and conflict styles. Throughout, they will apply these skills to their own institutional settings, using tools like NSQIP-P reports and to identify opportunities for change.

**Table 2 Tab2:** Facilitation training modules and content

Module	Content
De-implementation in ASP	• Overview of implementation science and the role of ASPs in change • Introduction to structured change strategies (e.g., order sets, facilitation) • Real-time reflection on current practices and data
Understanding the Evidence	• Review of current guidelines (e.g., WHO, SHARPS) • Analysis of NSQIP-P data and surgeon perspectives • Use of anecdotal evidence and local outcomes to drive change
Understanding Context	• Introduction to hospital context and relevant frameworks • Identification of site-specific barriers and opportunities • Structured activity to assess local capacity for improvement
Honing Facilitation Skills	• Assessment and reflection on communication and conflict styles • Exploration of team dynamics and facilitative leadership • Application of styles to support ASP initiatives
Presenting Evidence & Visualization	• Techniques for presenting data persuasively to clinical teams • Principles of effective evidence visualization • Guidance on pitching interventions and forming multidisciplinary teams
Wrap-Up and Next Steps	• Review of key takeaways • Guidance for applying workshop lessons at participants' institutions • Follow-up opportunities through collaborative meetings and study participation

Participants will also learn techniques for presenting and visualizing evidence to effectively influence surgical colleagues and promote team-driven, sustainable practice improvements. The live webinar will be offered quarterly over a two-year period, training approximately 20 participants per session. An asynchronous version, including recorded content, complementary materials, and interactive activities, will be available through the Nationwide Children’s Hospital CME website for ongoing access. Completion of the training provides access to quarterly collaborative meetings and the opportunity to contribute to ongoing data collection as part of the broader study.

Similarly, we will provide an asynchronous version of the workshop that will include pre-recorded presentations, activities, and opportunities to engage with Operatic community who have also participated in the workshop.

